### Implementation {16c}

Randomisation will be performed by a study team in the operation theatre. Names of this team member and the operating surgeon are noted as these team members are unblinded. They will not be involved in the outcome assessment of the trial.

## Assignment of interventions: blinding

### Who will be blinded {17a}

Blinding will be performed according to the evidence-based guidelines published by Probst et al. [33].A.Patients are blinded as they are under general anaesthesia during the trial intervention. Neither the discharge letter nor the operation report will contain any information regarding group allocation. This will be monitored by the clinical monitor.B.Surgeons performing the operation are unblinded to the trial intervention. To minimise performance bias, randomisation is performed after the closure of the posterior wall of the abdomen.C.For blinded outcome assessment, the person performing randomisation and the surgical team conducting the control/experimental intervention (“unblinded” study members) will be documented. All outcome assessments must be performed by blinded clinical assessors *not* being part of this group. This must be documented and will be verified by the clinical monitor.D.The trial statistician is blinded as she/he has no access to unblinded data during the study. Furthermore, the statistician will perform according to a pre-defined statistical analysis plan which will be finished prior to database closure.E.For primary endpoint evaluation, a clinical as well as radiological examination needs to be performed. Clinical outcome assessment must be performed by a surgeon. Blinding the radiologic examination can be achieved easily, as these physicians are not part of the prior trial interventions or the clinical trial centre. For clinical evaluation, the same prerequisites apply as outlined above, i.e. surgeons performing the clinical evaluation must be independent of the “unblinded” trial team.

### Procedure for unblinding if needed {17b}

Unblinding can be performed if medically indicated by the treating surgeon with the help of an unblinded study team member. Unblinding will be documented and reported to the steering group of the trial.

## Data collection and management

### Plans for assessment and collection of outcomes {18a}

The trial will be performed by the Clinical Trial Network of the German Society of Surgery (CHIR-Net, www.chir-net.de). The CHIR-Net has successfully performed trials with similar indications and recruitment rates [34–36]. All trial sites have already successfully participated in surgical clinical trials and have the necessary expertise, equipment and personnel to perform this trial.

### Plans to promote participant retention and complete follow-up {18b}

In order to minimise loss to follow-up, the following measures have been implemented:A pragmatic trial design with high-external validity, meaning that trial sites will have little problems to adapt their standard clinical workflow to the follow-up visitsFinancial reimbursement of travel costs for patients covering additional costs for trial-specific visitsAll trial sites are trained in performing surgical clinical trials (CHIR-Net) and have successfully participated in similar trialsOnly high-volume trial sites committing to include at least 10 patients per year will be chosen as trial sites

### Data management {19}

All protocol-required information collected during the trial must be entered by the investigator, or designated representative, in the eCRF. The investigator, or designated representative, should complete the eCRF pages as soon as possible after information is collected, preferably on the same day that a trial subject is seen for an examination, treatment or any other trial procedure. Any outstanding entries must be completed immediately after the final examination. An explanation should be given for all missing data. Further protocol deviations are explicitly asked for in the eCRF and have to be described by trial centres. The completed eCRF must be reviewed and signed by the investigator named in the trial protocol or by a designated sub-investigator.

The IMBI is responsible for the data management within the trial. The study data will be collected and managed using REDCap (Research Electronic Data Capture) [37], a secure, web-based data capture application hosted at the IMBI. To assure a safe and secure environment for the data acquired, data transmission is encrypted with secure socket layer (SSL) technology. Only authorised users are able to enter or edit data, and the access is restricted to data of the patients in the respective centre. All changes to data are logged with a computerised timestamp in an audit trail. All data will be pseudonymised. To guarantee high data quality, data validation rules will be defined in a data validation plan. Completeness, validity and plausibility of data will be checked in time of data entry (edit-checks) and using validating programmes, which will generate queries. If no further corrections are to be made in the database, eCRF data will be locked. Data will finally be downloaded and used for statistical analysis. All data management procedures will be conducted according to written defined standard operating procedures (SOPs) of the IMBI that guarantee an efficient conduct complying with GCP. At the end of the study, the data will be transformed into different data formats (e.g. csv-files) for archiving and to ensure that it can be re-used.

### Confidentiality {27}

The data protection concept stipulates that patients are only included in the study after they have been informed and after having signed the informed consent form (ICF). They will be informed as to the strict confidentiality of their data, but that their medical records may be reviewed for trial purposes by authorised individuals other than their treating physician. It is the responsibility of the investigator to maintain patients’ confidentiality. During the trial, patients will be identified solely by means of their individual identification code, and participating patients’ data will be recorded only in pseudonymised form. Trial-specific documents will be stored in accordance with local data protection law/ICH-GCP guidelines and will be handled in the strictest confidence. For the protection of these data, organisational procedures are implemented to prevent the distribution of data to unauthorised persons. Each trial site will maintain a personal subject identification list (screening numbers with the corresponding subject names) to enable records to be identified. The patients’ data will be transferred in a pseudonymised form from the trial centre to cooperating partners (coordinating investigator, data management). Names and all confidential data of participating patients will be handled in line with the obligations of medical secrecy, the European General Data Protection Regulation GDPR (Datenschutzgrundverordnung, DSGVO), the Federal Data Protection Act (Bundesdatenschutzgesetz) and the state Data Protection Act (Landesdatenschutzgesetz). Third parties have no access to original documents. After completion of the trial, data collected during the study will be kept on file for 10 years. It is guaranteed that the data protection provisions are followed.

### Plans for collection, laboratory evaluation and storage of biological specimens for genetic or molecular analysis in this trial/future use {33}

No plans for collection, laboratory evaluation and storage of biological specimens for genetic or molecular analysis are implemented in the P.E.L.I.O.N. trial.

## Statistical methods

### Statistical methods for primary and secondary outcomes {20a}

In the Addendum to the ICH E9 guideline, the estimands framework is recommended as a clear and transparent definition of “what is to be estimated” (International Council for Harmonization, 2019). In the following, the primary estimand corresponding to the primary objective is described:*Treatment*: Abdominal wall closure during loop ileostomy closure with a continuous slowly absorbable suture reinforced with a retromuscular non-absorbable, macro-pore (pore size ≥ 1000μm or effective porosity >0%) light-weight monofilament (class Ia) or mixed structure (class Ic) mesh (experimental arm) vs. abdominal wall closure during loop ileostomy closure with a continuous slowly absorbable suture*Population*: The targeted population is defined through the inclusion and exclusion criteria*Variable*: Incisional hernia (IH) within 24 months after intervention as defined by the European Hernia Society*Intercurrent events (ICEs):*Re-laparotomy affecting the loop ileostomy closure site without prior observation of IH: This event is exceedingly unlikely because the presence/absence of an IH will be observed at the time of re-laparotomy. Nevertheless, re-laparotomy affecting the loop ileostomy closure site without prior observation of IH presents a potential ICE. This is assumed to be independent of the intervention but influences the probability of IH occurrence. Since the estimate of interest is the treatment effect as if no re-laparotomy had been performed, the later occurrence (or lack thereof) of IH will not be considered. Instead, the primary endpoint will be imputed equivalently to patients who dropped out or were lost to follow-up, i.e. by multiple imputation. This handling conforms to a hypothetical strategy.Surgical site infections: Will not be considered, reflecting a treatment policy approach.Treatment switching: Will not be considered, reflecting a treatment policy approach. The risk of switching patients has been minimised through the choice of inclusion and exclusion criteria. However, switching may be needed due to clinical reasons getting obvious during surgery (e.g. mesh implantation technically not possible, mesh implantation necessary due to parastomal hernia)Death without prior observation of IH: Assuming independence of closure with or without mesh and death, the event is handled using the hypothetical strategyOncological systemic treatment therapy before or after the surgical intervention (e.g. chemotherapy): Systemic therapy is assumed to be unlikely to affect the primary endpoint. Reflecting a treatment policy, adjuvant therapy will be ignored*Summary measure: Differences in incisional hernia rates*

The hypotheses to be assessed in the primary efficacy analysis are as follows: 𝐻_0_: 𝑝_T_ = 𝑝_C_ and 𝐻_1_: 𝑝_T_ ≠ 𝑝_C_, where 𝑝_T_ and 𝑝_C_ denote the IH rates in the intervention and control groups, respectively.

The confirmatory analysis of the primary efficacy endpoint corresponds to the primary estimand defined in chapter 1.5. and will be done based on the full analysis set (FAS) according to the intention-to-treat principle. The FAS consists of all randomised patients and the patients will be considered in the group randomised to. The level of significance is set to 5% (two-sided).

The IH rates will be compared via a mixed logistic regression model including the factors treatment group and IH risk (high vs. low) as fixed effects and centre as a random effect. As the number of centres is relatively large in relation to the sample size, inclusion of the centre as a random effect instead of a fixed effect is indicated. Differences between centres cannot be ruled out but are of no special interest in the primary analysis; inclusion of centre as the random effect is recommended [38]. Besides this, the interpretation is more straightforward because “[…] in the context of RCTs, centre effects can be regarded as a nuisance parameter, as the primary goal is to estimate the treatment effect”. For the structure of the covariance matrix of the random intercept of centre, a variance component structure is used allowing for different variability within each centre while assuming that centres are independent. Missing data for the primary outcome variable due to dropout or loss to follow-up are assumed to be at least “missing at random” and will be replaced by using multiple imputation. Occurrence of IH after the ICE re-laparotomy affecting the loop ileostomy closure site and death without prior observation of IH will be imputed the same way. Information whether a patient was event-free regarding the occurrence of an IH before loss-to-follow-up, dropout or the respective ICEs will be included into the multiple imputation procedure. This will be done by imputing the primary endpoint “incisional hernia within 24 months” (yes/no) using the variable “incisional hernia within 12 months” (yes/no) besides treatment group, IH risk (high vs. low) and centre using the fully conditional specification (FCS) and the discriminant function method. ICEs that are handled using a treatment policy strategy will be ignored in the primary analysis. The proportion of each ICE will be described by group to support the interpretation of the primary effect estimate.

Sensitivity analyses regarding the imputation method and the underlying assumptions will be performed. These include applying a pattern mixture model under the assumption of a “missing not at random” data mechanism, as well as best- and worst-case scenarios to assess the robustness of the results.

Within a sensitivity analysis, oncologic treatment will be included into the logistic regression model for the primary endpoint as an additional covariate.

The complementary estimands will be estimated using the same primary analysis strategy as used for the primary estimand with the following differences: To estimate the first complementary estimand, the primary endpoint in the switched patients will not be taken as observed but will be imputed in the group as treated. The second complementary estimand will be estimated based on all patients treated as randomised (treatment switcher will be excluded). In the following, supplementary analyses for the primary estimand are described.

The same test as in the primary analysis will be conducted in the per-protocol set (PP, based on those patients without major protocol violation). Failure to respect the exclusion criteria or to follow the technical aspects of the assigned study group (suture material, stitch technique, used mesh) will be considered as major protocol violations. Analyses in the PP set are known to be biased and do not correspond to any estimand and thus have to be interpreted with great caution. Based on the FAS set, a complete case analysis will be performed without imputation of missing data.

All baseline variable and secondary outcomes will be evaluated descriptively, and descriptive *p-*values are reported together with 95% confidence intervals for the corresponding effects. As in the primary analysis, secondary endpoints will be assessed by a mixed regression model including the treatment group as a fixed effect and centre as a random effect. For each endpoint, relevant covariates which will be included in the analysis are pre-defined.

The safety analysis includes the calculation of frequencies and rates of complications (specific secondary outcome parameters) together with 95% confidence intervals. This analysis will be based on the safety set that contains all randomised patients in the group as treated.

All analyses will be done using SAS version 9.4 or higher.

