## Introduction

### Background and rationale {6a}

Diverting loop ileostomy is used in colorectal surgery to reduce the consequences of leakage of a bowel anastomosis. According to the Federal Statistical Office of Germany, approximately 15,000 diverting loop ileostomies and 11,500 loop ileostomy closures are performed annually in Germany [1]. The timepoint of ileostomy reversal is debated [2, 3]. Parastomal hernia is frequent after ostomy creation and is estimated to be over 30% by 12 months, 40% by 2 years and 50% or higher at longer duration of follow-up [4, 5]. After primary closure of ileostomy sites, approximately 20% of patients develop an incisional hernia (IH) at the site of stoma reversal within 12 months and up to one-third within 2 years [6] as the incidence of IHs increases over time [7].

Multiple studies have shown that IH causes substantial morbidity and a reduction in the quality of life due to abdominal pain and discomfort, a reduction in the daily activity as well as mortality [8]. Furthermore, IH can cause potentially life-threatening complications with bowel incarceration and strangulation. Furthermore, recurrence of IH following IH repair, which occurs in up to 40% of patients [9], is associated with decreased quality of life [10]. IH causes a substantial burden to healthcare systems worldwide [11, 12]_ and an estimated annual cost of 8.2 million € for the German healthcare system [13].

Because of the important consequences for patients and national healthcare systems, the prevention of incisional hernia has been a subject of intensive investigation over the last decades. For ventral IHs, prophylactic mesh placement at the time of abdominal wall closure is now an accepted technique. Its efficacy has been tested in numerous randomised controlled trials (RCTs) [13–15].

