### Sample size {14}

Sample size calculation is based on the rate of the primary endpoint (IH rate) within 24 months after surgery. Based on the assumption that the percentage of patients developing an IH in the control group is 30% (4–7), we hypothesise a reduction to 15% in the intervention arm (conservative reduction rate below that reported in the above-mentioned trials). Consequently, a sample size per group of 121 patients is needed for the group comparison by the chi-squared test to achieve 80% power in detecting this difference in IH rate at a two-sided level of significance of 5%. It is assumed that using a logistic regression model adjusting for IH risk (low-risk vs. high-risk patients: BMI ≥ 27) and including centre as a random effect in the primary analysis will lead to less unexplained variance and thus to an increased power.

The intercurrent event re-laparotomy affecting the loop ileostomy closure site and death without prior observation of IH are expected to be very rare, with just a few patients each. Based on previous trials, to account for the loss of information, a rate of 20% of dropouts, loss to FU and relevant ICEs (handled with the hypothetical strategy) is considered. Therefore, a total of 304 patients (152 per group) will be randomised. The other ICEs are ignored in the primary estimand and not accounted for in the sample size calculation. Calculation was performed using PASS 16.0.12. Only high-volume trial sites committing to include at least 10 patients per year will be chosen as trial sites.

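### The discriminant-function imputation gives patients hernia-free at 12 months almost no later hernia risk, which understates both 24-month rates and shifts their difference (about 1 of 15 points if loss is similar in both arms)

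*Protocol article*

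**What the plan says.** In the protocol article, Statistical methods for primary and secondary outcomes {20a}, 24-month outcomes missing through dropout or loss to follow-up are assumed missing at random and multiply imputed. Two intercurrent events (re-laparotomy at the closure site, and death without a prior hernia) are imputed the same way. The yes/no 24-month endpoint is predicted from yes/no hernia status at 12 months, "besides treatment group, IH risk (high vs. low) and centre using the fully conditional specification (FCS) and the discriminant function method". The stated aim is to use the knowledge that a patient was event-free before leaving. The same section names the difference in hernia rates as the summary measure, and the confirmatory test is the treatment term of a mixed logistic model.

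Background and rationale {6a} gives a hernia rate of about 20% "at the site of stoma reversal within 12 months and up to one-third within 2 years". Sample size {14} states that "a rate of 20% of dropouts, loss to FU and relevant ICEs (handled with the hypothetical strategy) is considered".

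**The concern.** A linear discriminant assumes that, within each outcome class, the predictors are normal with one shared covariance. Here 12-month status is nested in the endpoint: it is always 0 in the no-hernia class and mostly 1 in the hernia class. The pooled fit therefore becomes very steep in this variable.

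A patient with a hernia at 12 months already has the endpoint and needs no imputation. Among patients seen at 12 months, those imputed are the ones free of hernia at that visit, and the misfit falls on them. Late hernias are the reason for 24-month follow-up, and they are what the imputation should restore. If it does not restore them, the reported rates and their difference are biased even when the missing-at-random assumption is true.

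**Working it through.** **1. The plan's own figure.** The inputs from Sample size {14} are: "percentage of patients developing an IH in the control group is 30" per cent; "we hypothesise a reduction to 15% in the intervention arm"; "to achieve 80% power in detecting this difference in IH rate at a two-sided level of significance of 5" per cent.

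n = [1.96·√(2·0.225·0.775) + 0.8416·√(0.30·0.70 + 0.15·0.85)]² / 0.15² = (1.157 + 0.489)² / 0.0225 ≈ 120.5, so 121. This matches "a sample size per group of 121 patients is needed for the group comparison by the chi-squared test". Then 121/0.80 = 151.25, so 152 per arm, which matches "a total of 304 patients (152 per group) will be randomised". The planning figures reproduce and are used below.

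**2. Share *s* of 24-month hernias already present at month 12.** The background rates give 20/33 = 0.61 to 20/30 = 0.67. I take *s* = 2/3 in both arms, with a range of 0.50 to 0.80. The protocol gives no 12-month rate for mesh, so an equal share in both arms is an assumption.

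**3. True risk after a clear 12-month visit,** p(1−s)/(1−ps):
- Control: 0.10/0.80 = 12.5%.
- Mesh: 0.05/0.90 = 5.6%.

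**4. Risk under the discriminant model.** Pool the arms (π = 22.5%) and use 12-month status alone. The class means are *s* and 0, and the pooled variance is π·s(1−s). At 12-month status 0:

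logit P = log[π/(1−π)] − s/[2π(1−s)]

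For *s* = 2/3 this is −1.237 − 4.444 = −5.681, so P = 0.3%. The true pooled value is 0.075/0.85 = 8.8%.

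| *s* | discriminant | true |
|---|---|---|
| 0.50 | 3.1% | 12.7% |
| 0.60 | 1.0% | 10.4% |
| 0.67 | 0.3% | 8.8% |
| 0.80 | <0.01% | 5.5% |

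A simulation of the stated procedure used 304 patients, posterior draws, 10 centres, and centre and risk group unrelated to outcome. At *s* = 2/3 it imputed hernias in 1.1% (control) and 0.5% (mesh) of these patients. At *s* = 0.50 the figures were 5.3% and 2.3%, against true values of 17.6% and 8.1%.

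**5. Effect on the rates, 20% loss in each arm.** By hand at *s* = 2/3:
- Control: 0.80 × 0.20 × (0.011 − 0.125) = −1.8 points.
- Mesh: 0.90 × 0.20 × (0.005 − 0.056) = −0.9 points.

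Pure carry-forward would give 30 − 0.20×10 = 28.0% and 15 − 0.20×5 = 14.0%, a difference of 14.0 points. Simulated bias against the same data without missing values, in points:

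| *s* | control | mesh | difference |
|---|---|---|---|
| 0.50 | −2.0 | −1.1 | −1.0 |
| 0.60 | −2.1 | −1.0 | −1.1 |
| 0.67 | −1.9 | −1.0 | −1.0 |
| 0.80 | −1.2 | −0.6 | −0.6 |

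If those lost also missed month 12 (*s* = 2/3), the bias is −1.8 / −0.7 / −1.1. Imputing by arm from the observed rate among patients free at 12 months leaves a bias of about 0.1 point or less.

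**6. The tested effect.** The log odds ratio for 30% vs 15% is −1.735 + 0.847 = −0.887. For 28% vs 14% it is −1.815 + 0.944 = −0.871, a change of under 2%. Simulation (unadjusted model, 152 per arm) gave −0.88 against −0.89 with complete data. Power was 86%, against 85% with imputation among patients free at 12 months.

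**7. Unequal loss (*s* = 2/3).** Bias of the 15-point difference:
- 30% control / 10% mesh loss: −2.2 points.
- 15% / 25%: −0.2 points.
- 10% / 30%: +0.4 points.

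With no true effect (30% in both arms) and 10% / 30% loss, a spurious mesh benefit of 1.7 points appeared (1.6 in a second run).

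**The case against.** The strongest reply is that the confirmatory test hardly notices. Both rates shrink nearly in proportion, so the odds ratio and power stay almost as they were. With similar loss, the 1-point bias in the difference is conservative and small beside a standard error of about 4.6 points. All of this stands, and it limits the severity.

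The plan also has sensitivity analyses on the imputation method, a missing-not-at-random model, best and worst cases, and a complete-case analysis. These would expose the problem, but none replaces the confirmatory estimate. The protocol expects low loss, and its 20% allowance also covers patients who miss both visits. Lower loss shrinks the bias roughly in proportion.

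Two stronger readings are tempting:

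- **Standard errors that are too small.** A reader might infer this because the imputations hardly vary: the between-imputation share of variance is under 1%, against 9–10% with imputation among patients free at 12 months. It does not follow. Near-carry-forward turns the endpoint into an ordinary binary variable with rates of 28% and 14%. Its binomial standard error is √[(0.28·0.72 + 0.14·0.86)/152] = 0.046, which is right for that (biased) estimator. Simulated mean standard errors matched or exceeded the empirical spread at 20% loss (risk difference 0.046 vs 0.043; log odds ratio 0.300 vs 0.280 and, in another run, 0.299 vs 0.293). At 30% loss they were close (0.304 vs 0.310). With no effect and equal loss, rejection was 4.3%. One run showed interval coverage of 93% against 95%, a slight loss.
- **A difference that is always biased downward.** This needs similar loss in both arms, as step 7 shows. Even at 10% / 30% loss with no effect, rejection rose only to 6.1%, and nothing in the protocol predicts such an imbalance.

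**Conclusion.** The point holds in a limited form and should be fixed. The named method contradicts its own purpose: under the missing-at-random assumption that the protocol makes, it imputes away most late hernias. At the planning rates, with 20% loss in each arm, about 30% / 15% / 15 points become about 28% / 14% / 14 points. The loss in the difference is 0.6 to 1.1 points over the range of *s* examined.

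This matters because the difference in rates is the declared summary measure, and because the result leans towards whichever arm loses more patients. It does not threaten the power or the standard errors of the confirmatory test when loss is similar.

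The size rests on three assumptions: the same 12-month share in both arms, 12-month status entering the discriminant function as the text says, and loss near the planned 20%. The near-zero imputed risk (about 1% or less) applies at the share the background implies. At a share of 50% the imputed risk is higher, but still far below the truth.

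**What to change.** Replace the sentence on the imputation method with three rules:

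1. Any hernia observed by 12 months keeps the 24-month endpoint at 'yes'. This already follows from the endpoint definition, but should be written into the imputation step.
2. Among patients free at 12 months, impute the 24-month endpoint by logistic regression on treatment, IH risk and centre.
3. If month 12 is also missing, impute it first by logistic regression, then apply rules 1 and 2.

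Restricting rule 2 to patients free at 12 months removes the perfect prediction by 12-month status that an ordinary logistic imputation would meet.

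The cost is wording, a few lines of code and a slightly wider standard error (0.049 against 0.046 for the risk difference). No new data are needed, and the change can be made before the analysis plan is finalised. One detail needs settling: at *s* = 2/3, late hernias number about 152×0.10 + 152×0.05 ≈ 23, of which about 18 would be observed at 20% loss. Spread over 10 or 13 centres, some centres may have none, so the plan should say how centre is then handled, for example by pooling small centres.
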